**Sub Study B (Group IV-V)**

**Visit 1. (D0) 1st blood sample & 1st vaccination**

- a. Provide parent/guardian(s) with the relevant information concerning the trial.
- b. Obtain informed consent, dated and signed by the parent/guardian(s).
- c. Check eligibility criteria.
- d. Perform a physical examination.
- e. Allocate an inclusion number chronologically to the enrolment of the subject.
- f. Take a pre-vaccination blood sample (V1, 4 ml).
- g. Inject the 1st dose of the quadrivalent influenza vaccine
- h. Put the initial name and the inclusion number of the subject on the used vial.
- i. Record the batch of vaccine in the CRF and the list of participant.
- j. Keep the subject under observation for 30 minutes and evaluate the immediate local reactions and systemic events.
- k. Complete CRF.
- l. Provide a diary card (DC1) to the subject or parent/guardian (s) and inform them how to use and fill the diary card.
- m. Inform the parent/guardian(s) that they should contact the investigator or the study nurse in case of any Serious Adverse Event.
- n. Instruct the parent/subjec (s) to return for visit 2.

⇒ **Visit 2 (V1 + 28 (-4/+7) days) 2nd injection**

- a. Perform a physical examination
-

- 
- b. Check the possible Serious Adverse Events, which occurred since the last visit.
  - c. Record the safety data from DC1 to CRF.
  - d. Check the concomitant therapies and record in the CRF.
  - e. Inject the 2nd dose of the quadrivalent influenza vaccine.
  - f. Put the initial name and the inclusion number of the subject on the used vial.
  - g. Record the batch of vaccine in the CRF and the list of participant.
  - h. Keep the subject under observation for 30 minutes and evaluate the immediate local reactions and systemic events.
  - i. Complete CRF.
  - j. Provide the diary card (DC2) to the parents, and inform them how to use and fill the diary card.
  - k. Inform the subject's parents that they should contact the investigator or the study nurse in case of any Serious Adverse Event.
  - l. Instruct the parents to return for visit 3.

⇒ **Visit 3. (V2+28 days (-4/+7) days) 2nd blood sample**

- a. Perform a physical examination.
- b. Check the possible Serious Adverse Events, which occurred since the last visit.
- c. Record the safety data from DC2 to CRF.
- d. Check the concomitant therapies and record in the CRF.
- e. Take a post-vaccination blood sample (V3, 4 ml).
- f. Complete CRF.
- g. Completion the study.

### **5.3. Conditions for Withdrawal from the Trial**

The investigator may decide to discontinue the treatment (i.e. vaccination), should an event which is considered as a definite contra-indication, is occurred during the trial.

### **5.4. Lost to Follow-up Procedures**

In case of subjects failed to visit for a follow-up examination, extensive effort should be taken to locate or recall them or at least to determine their health status. These efforts should be documented in the subject's CRF and source documents.

### **5.5. Termination Classification**

Definitions:

- Discontinuation by the investigator: an observation is considered a discontinuation by the investigator when the latter decides to terminate the subject's participation for medical reasons (for subject's safety), for personal reason (it is his opinion that the subject can not continue to participate), etc.
-

- 
- Drop-out: a subject included in the trial is said to have dropped out after deciding, on his own volition, to terminate his participation in the trial. Subjects may decide to withdraw their subject from the trial at any time. The investigator should make sure, however, that withdrawal was not due to an adverse event. The reason for withdrawal should be noted in the space provided for this purpose in the CRF.
  - Lost to follow-up: the subject could not be found in spite of the investigator's researches.
  - Death.

## **5.6. Monitoring, Auditing and Archiving**

### **5.6.1. Routine Monitoring**

#### **5.6.1.1. Set-up Visit**

A set-up visit will be performed before the inclusion of the first subject in the center. The monitor and/or the Medical Responsible will verify and document that the material to be used during the trial has been received and that the investigational team has been properly informed about the trial, regulatory requirements and the SOPs established by Bio Farma.

#### **5.6.1.2. Follow-up Visit**

The Monitor will carry out regular follow-up visits.

The investigator commits himself to be available for these visits and to allow the monitoring staff direct access to subject medical file and CRFs. The Monitors are committed to professional secrecy.

During the visits, the Monitors:

- will carry out a quality control of the trial progress: respect to protocol and operating guidelines, data collection, signature of consent forms, sample and product management, cold chain monitoring, completion of document and appearance of SAE,
- will check the CRFs and other documents,
- assess the inclusions in order to evaluate the number of complete or ongoing observations.

Monitors will discuss any problem with the investigator and define, after consultation, the actions to be taken. Once the CRFs corresponding to the last visit have been returned duly completed and signed, the investigator must be available to continue the filling out of the correction sheets transmitted by the Monitor, if necessary, until the database is locked.

---

---

#### **5.6.1.3. Close-out visit**

A close-out visit will be performed at the end of the trial. Its goals are to make sure that:

- the center has all the documents necessary for archiving,
- all samples have been shipped,
- all unused material has been recovered,
- all products have been returned to the sponsor.

#### **5.6.2. Audits and Inspections**

If necessary, a quality assurance audit could be carried out by Bio Farma Quality Assurance Department or by independent auditors to make sure that the trial has been conducted according to the protocol and the applicable regulations. An inspection may be conducted by Indonesian Regulatory Authorities. The investigator shall allow direct access to trial documents.

#### **5.6.3. Archiving**

The investigator must keep all trial documents provided by Bio Farma for **at least 5 years** after the completion or discontinuation, whatever the center (private, hospital, institution). The investigator will inform Bio Farma of any address change.

---

---

## 6. Adverse Event Reporting

### 6.1. Definitions

#### ⇒ Adverse event (AE):

Any untoward medical occurrence in a patient or clinical investigation subject administered a pharmaceutical product and which does not necessarily have to have a causal relationship with this treatment.

An adverse event can therefore be any unfavorable and unintended sign (including an abnormal laboratory finding, for example), symptom or disease temporally associated with the use of a medicinal product, whether or not considered related to the medicinal product.

#### ⇒ Serious adverse event (SAE):

A serious adverse event (experience) is any untoward medical occurrence that at any dose:

- results in death,
- is life-threatening. The term “life-threatening” in the definition of “serious” refers to an event in which the patient was at risk of death at the time of the event; it does not refer to an event, which hypothetically might have caused death, if it were more severe.
- requires inpatient hospitalization or prolongation of existing hospitalization,
- results in persistent or significant disability/incapacity, or
- is a congenital anomaly/birth defect.

Medical and scientific judgment should be exercised in deciding whether expedited reporting is appropriate in other situations, such as important medical events that may not be immediately life-threatening or result in death or hospitalization but may jeopardize the patient or may require intervention to prevent one of the other outcomes listed in the definition above. These should also usually be considered serious.

#### ⇒ Adverse drug reaction (ADR):

All noxious and unintended responses to medical product related to any dose should be considered adverse drug reactions. The phrase “responses to a medicinal product” means that a causal relationship between a medicinal product and an adverse event is at least a reasonable possibility, i.e. the relationship cannot be ruled out.

---

---

⇒ Unexpected adverse drug reaction:

An adverse reaction, the nature or severity of which is not consistent with the applicable product information (e.g. Investigator's Brochure for an unapproved investigational medicinal product).

## **6.2. Expected Reactions**

Anticipated reactions to the trial vaccines are those expected for Influenza HA vaccines and should be mild and transient. Reactions that have been reported may be found in the package insert of Influenza HA vaccine.

## **6.3. Safety Data Collection and Management Procedures**

The safety data will be collected up to one month after the one injection. During this period, each patient will be provided with a diary card to record the appearance, the duration and the intensity (coded 1,2 or 3) of any local reaction and any systemic event expected or not. The intensity of local reactions will be assessed using a plastic bangle presented in Appendix 4.

For any subject, a local reaction is defined as the occurrence of one or several reaction(s) (expected or unexpected) at the injection site within 28 days following vaccination. Local reactions are:

- ↳ **Local pain**
- ↳ **Redness**
- ↳ **Induration**
- ↳ **Swelling**
- ↳ **Other local reactions**

For any subject, a systemic event is defined as the occurrence of one or several symptom(s) (solicited and unsolicited) within 28 days following vaccination. Systemic events are:

- ↳ **Fever** (axillary temperature  $\geq 38^{\circ}\text{C}$ )
- ↳ **Fatigue**
- ↳ **Muscle pain (Myalgia)**
- ↳ **Other systemic events**

Parents/subjects will measure the intensity of local reactions in using a plastic bangle (See appendix 4). The intensity will be coded in the Diary and CRF as follows:

---

---

|                                                                 | 1=Mild                                      | 2=Moderate                                                  | 3=Severe                                        |
|-----------------------------------------------------------------|----------------------------------------------------|--------------------------------------------------------------------|--------------------------------------------------------|
| Local pain for infants and children (6-35 months)        | Reacts when site is touched                        | Cries when site is touched                                         | Cries when limb is moved                               |
| Local pain for subjects <math>\geq 3</math> years of age | Mild pain to touch                                 | Pain with movements                                                | Significant pain at rest                               |
| Redness/swelling/Induration
Other local reactions    | Reaction completely included in the smaller circle | Largest diameter of the reaction included between the two circles  | Reaction beyond the largest circle                     |
| Fever                                                    | 38.0 – 38.4°C                                      | 38.5 – 38.9°C                                                      | > 39.0°C                                               |
| Fatigue
Myalgia                                      | No interference with activity                      | Some interference with activity                                    | Significant prevents daily activity                    |
| Other systemic events                                    | No interference with activity                      | Some interference with activity not requiring medical intervention | Prevents daily activity, requires medical intervention |

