#### **7.2.2. Parameters to be measured**

a. GMT, seroprotection and seroconversion rates before and after one dose of immunization will be described per antigen per group vaccine with 95% confidence interval (CI).

b.1 Local reactions and systemic events occurring within 30 minutes after vaccination, 72 hours after vaccination and unexpected event rates, which occurred after 72 hours will be assessed per antigen and per group vaccine with 95% CI.

Any Serious Adverse Events occurring over the study period will be described.

**Subjects** will record the presence of any local or systemic symptom within 28 days following each injection in the diary card. They will answer all questions in the diary for expected and unexpected events during this period.

**The investigator** will report the following data in the CRF:

- The start and end dates of all events.
- The severity (code 1, 2 or 3) of all local reactions.
- Site of local reactions.
- The severity (code 1, 2 or 3) of all systemic events.
- The exact daily maximal axillary temperature up to 3 days after the vaccination.
- The exact maximal axillary temperature of any other fever period.
- The action taken.

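### Section 6.3 adapts local pain to ages 6–35 months but not the non-fever systemic events, so these may be under-recorded in Group IV

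*Protocol*

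**What the plan says.** Section 6.3 defines systemic events once, for everyone: "For any subject, a systemic event is defined as the occurrence of one or several symptom(s) (solicited and unsolicited) within 28 days following vaccination". Three events are named: fever (by axillary temperature), fatigue and "Muscle pain (Myalgia"). The fourth entry is the open category "Other systemic events".

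The intensity table in Section 6.3 puts fatigue and myalgia in one row, graded by how far they interfere with activity; the severe grade reads "Significant prevents daily activity". The open category has its own three grades, which also turn on activity and add the need for medical intervention.

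The same table has a separate row, "Local pain for infants and children (6-35 months"), in which the grades are behaviours a parent can watch: a reaction to touch, crying at touch, and crying on movement of the limb. Appendix 3 also gives Groups I, IV and V a smaller bangle for measuring visible local reactions.

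On scope, the diary is to capture "any local reaction and any systemic event expected or not". Section 7.2.2 adds: "They will answer all questions in the diary for expected and unexpected events during this period". In Sub-study B the parents receive the diary and are told how to complete it (Section 5.2).

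**The concern.** The protocol recognises that a child under three cannot rate pain and replaces self-report with observable behaviour, but only for local pain. Myalgia is a felt symptom that a parent of a pre-verbal infant cannot identify. Fatigue can at best be inferred from behaviour, and interference with activity has no infant wording. The signs a parent would notice, such as irritability, abnormal crying, drowsiness, poor appetite or vomiting, are not named in Section 6.3. As far as that section shows, they have to enter through the open category.

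This matters because safety in all subjects is a secondary objective (Section 2.2) and Section 8.1.3.2 tabulates how often each type of systemic event occurs. In Group IV a low count for fatigue or myalgia could mean few events or poor detection, and the table would not tell the two apart. Sub-study B has no TIV arm, so no concurrent group would show the same loss. Section 1.5 reports no previous QIV study by the sponsor, and the Japanese QIV study it cites was in adults. Group IV is therefore the only source of QIV safety data below three years described in the document.

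**Working it through.** The point rests on the symptom list and the grading table. The protocol states no expected systemic event rate for infants, so there is no figure to reproduce.

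**1. Items of Section 6.3 side by side, for Group IV**

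| Item | Adapted to 6–35 months? | What the parent has to do |
|---|---|---|
| Local pain | Yes, own row | Watch the response to touch and limb movement |
| Redness, swelling, induration | Yes, smaller bangle (circles of 5 and 2.5 cm, against 10 and 5 cm for Groups II and III) | Size is read against the circles |
| Fever | Not needed | Read a thermometer |
| Fatigue | No | Infer it and judge interference with activity |
| Myalgia | No | Infer a felt symptom and judge interference with activity |
| Open systemic category | No | Report an event with no sign named in the section |

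The first three rows are usable in this age group. The last three are the non-fever systemic items, and none is adapted.

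**2. Other routes by which an event could be caught**

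- Section 3.6: phone follow-up of safety within 3 days of V1, and a diary for any systemic complaint. The only example given is weakness.
- Section 7.2.2: parents are interviewed about local and systemic reactions within 72 hours of each injection.
- Section 5.2: physical examination at V2 and V3.

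These routes make it more likely that an event is recorded. None names an infant sign to ask about. The sample form for reporting adverse events in Appendix 2 does name diarrhoea and vomiting, but Section 6.3 does not carry them into the systemic list.

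**3. How many subjects are affected**

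- Group IV: 135 subjects × 2 doses = 270 planned injections.
- Share of the trial: 135 / 810 = 16.7%. Share of Sub-study B: 135 / 270 = one half.

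**4. Illustration of what incomplete capture would do**

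The true rate and the capture fraction below are assumptions; the protocol gives neither for infants. Its only overall systemic rates are 16.3% (the 2008 study in adolescents and adults) and 8/55 = 14.5% (Japanese adults), both in Section 1.5.

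The expected count is x = 135 × true rate × capture fraction, rounded. The observed rate is x / 135. The exact 95% interval runs from the 0.025 quantile of Beta(x, 135 − x + 1) to the 0.975 quantile of Beta(x + 1, 135 − x).

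| Assumed true rate | Capture 100% | Capture 75% | Capture 50% |
|---|---|---|---|
| 10% | 14/135 = 10.4% (5.8–16.8) | 10/135 = 7.4% (3.6–13.2) | 7/135 = 5.2% (2.1–10.4) |
| 20% | 27/135 = 20.0% (13.6–27.7) | 20/135 = 14.8% (9.3–21.9) | 14/135 = 10.4% (5.8–16.8) |
| 30% | 40/135 = 29.6% (22.1–38.1) | 30/135 = 22.2% (15.5–30.2) | 20/135 = 14.8% (9.3–21.9) |

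The confidence interval reflects sampling error only. With an assumed true rate of 20% and half the events captured, the interval of 5.8–16.8% excludes the true rate, and nothing in the output would show it. The table shows that the effect could matter. It does not show that it will occur.

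**The case against.** The strongest reply is that the protocol already casts a wide net. The diary takes any event, expected or not. A parent keeps it, so the infant need not self-report. There is a phone call after V1, an interview about each injection and an examination at each later visit. Group IV runs to 35 months, and a parent of a two-year-old may well notice tiredness. The diary and CRF are not reproduced, and Section 7.2.2 says the diary contains questions on expected and unexpected events, so infant items may already be there.

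Much of this stands. A reader might infer that reactogenicity in Group IV as a whole lacks a usable instrument. That is not supported: fever, local pain and visible local reactions are all measured in a way that suits the age. A reader might also infer that systemic events will be understated, or that fatigue and myalgia will be close to zero whatever the vaccine does. The document supports a risk of under-ascertainment, not a certainty and not a size.

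On comparability, the safety contrasts that are named, QIV against TIV and batch against batch, belong to ages 9–40. Group IV also differs from the older groups in dose volume or number of doses, so only the general description between groups in Section 8.1.3.2 could set it beside them.

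What the reply does not remove is the asymmetry within Section 6.3. An open category prompts no named sign, and an interview with no listed signs does not standardise what is asked. If the diary does contain infant items, Section 6.3, which fixes how intensity is coded in the diary and CRF, has no specific grading row for them and needs to be aligned.

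**Conclusion.** The point holds in a limited form. The named non-fever systemic events and their grades are not adapted to 6–35 months, although local pain in the same table is. Non-fever systemic reactogenicity in Group IV, 135 subjects and 270 planned injections without a concurrent comparator, depends on parental inference and on entries that no named item prompts. It may be under-ascertained by an unknown amount, and its per-type frequencies should not be set beside those of older groups.

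This assumes that the diary and CRF follow Section 6.3; if they already hold infant items, only the protocol text needs correcting. The primary endpoint, and fever and local reactions in Group IV, are unaffected. This is an inexpensive improvement to data collection for a secondary, descriptive objective.

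**What to change.** In Section 6.3, the diary and the CRF, add for Group IV a set of named systemic items that a parent can observe, for example irritability, abnormal crying, drowsiness, loss of appetite and vomiting. Define grades 1–3 for each in observable terms, as the table already does for local pain. In Section 8.1.3.2, tabulate these separately from the list for subjects of 3 years and over.

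Fatigue and myalgia need not be removed for Group IV, since parents of the older children in the group may be able to report them, but they should not be read as the infant systemic profile. If the items cannot be added, the minimum is to state that non-fever systemic rates in Group IV rest largely on unprompted reports and will not be compared across age groups.

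The cost is about one extra diary/CRF page for one group, with no added visit or procedure. The downside is that more mild events will be recorded in Group IV.

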### 3.6. Subject Diaries and Interim Histories

Subjects will keep an observation card (diary) to assess and record information for local/systemic reactions for 28 days following immunization with special attention within the first three days. Safety data within 3 days after immunization (V1+3 days) will be followed up by phone.

The local reaction assessment will involve assessment of the vaccination site. The systemic event assessment will involve daily axillary temperature readings (subject/parent will be supplied with a thermometer and instructed how to use it) and recording any systemic complaints such as weakness on a diary. Any medical office

---

---

visit, emergency room visit or hospitalization for any reason will be recorded throughout the trial period. Moreover, any serious adverse event occurring throughout the trial period should be reported immediately and will also be recorded in the CRF.

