### 5.2. Visit Procedures

#### **Sub Study A (Group I-III)**

#### **Visit 1. (D0) 1st blood sample & 1st vaccination**

- Provide subject or parent/guardian(s) with the relevant information concerning the trial.
  - Obtain informed consent/and assent, dated and signed by the subject/parents.
  - Check eligibility criteria.
  - Perform a physical examination.
  - Allocate an inclusion number and randomization code, chronologically to the enrolment of the subject.
  - Take a pre-vaccination blood sample (V1, 4 ml).
  - Inject the 1st dose of the quadrivalent or trivalent influenza vaccine
  - Put the initial name and the inclusion number of the subject on the used vial.
-

- 
- i. Record the code of vaccine in the CRF and the list of participant.
  - j. Keep the subject under observation for 30 minutes and evaluate the immediate local reactions and systemic events.
  - k. Complete CRF.
  - l. Provide a diary card (DC1) to the subject or parent/guardian (s) and inform them how to use and fill the diary card.
  - m. Inform the subject/ parent that they should contact the investigator or the study nurse in case of any Serious Adverse Event.
  - n. Instruct the subject/ parent to return for visit 2.

⇒ **Visit 2 (V1 + 28 (-4/+7) days) 2nd blood**

- a. Perform a physical examination
- b. Check the possible Serious Adverse Events, which occurred since the last visit.
- c. Record the safety data from DC1 to CRF.
- d. Check the concomitant therapies and record in the CRF.
- e. Take a blood sample (V2, 4 ml)
- f. Completion of the study.

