### **Safety analysis**

At each follow-up visit, the following parameters will be computed:

- ◆ Percentage and number of subjects experiencing immediate reactions within 30 minutes of vaccinations.
- ◆ Number and percentage of subjects with at least one local reaction (within 72 hours after each injection), with the frequencies of each type of local reactions (global and broken down according to the size of the reaction when appropriate)
- ◆ Number and percentage of subjects with at least one systemic event (within 72 hours after each injection either related or non related to the vaccine), with the frequencies of each type of event (global and broken down according to the relationship and the severity)
- ◆ Number and percentage of subjects with at least one local reaction (within 72 hours to one month after each injection), with the frequencies of each type of local reactions (global and broken down according to the size of the reaction when appropriate)
- ◆ Number and percentage of subjects with at least one systemic event (within 72 hours to 1 month after each injection either related or non related to the vaccine), with the frequencies of each type of event (global and broken down according to the relationship and the severity)
- ◆ Number and percentage of subjects with at least one Serious Adverse Event, with the frequencies of each type of event (global and broken down according to the relationship and the severity of the event).
- ◆ Description between groups.

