### Appendix 3: Plastic bangle model

Group II (13-17 years old ) and

Group III (18-40 years old)

This bangle will be printed on a transparent plastic square and will be used to assess the intensity of local reactions, which may occur after the injection of vaccine. The bangle is composed of one 10 cm diameter circle and one 5 cm diameter circle. These two circles are concentric and the cross corresponds to the center of the circles.

This plastic bangle will be given to the health worker with instruction for use, as follows :

1. Place the cross at the center of the reaction (middle of the largest diameter, see diagram)
2. Do not press on the plastic square so as not to increase the diameter of the reaction.
3. Note the intensity (1, 2 or 3).

Intensity 1 and 2 are represented by the circle that completely encircles the largest diameter of the reaction. If the largest diameter of the reaction goes outside the biggest circle, the intensity is 3.

For example, in this figure, the intensity is coded 2.

[figure not shown]

---

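### Section 6.3 has families grade local reactions with the plastic bangle, but Appendix 3 issues it to the health worker and nothing supplies it to families, so the 72-hour size breakdown could rest on estimate or recall

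*Protocol*

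**What the plan says.** Section 6.3 of the Protocol assigns the measurement to the household: "Parents/subjects will measure the intensity of local reactions in using a plastic bangle". It then says "The intensity will be coded in the Diary and CRF as follows" and gives a table. For redness, swelling, induration and other local reactions, that table defines grades 1 to 3 by two circles; grade 1, for example, is "Reaction completely included in the smaller circle".

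Appendix 3 describes two bangles, one for Groups II and III and one for Groups I, IV and V. On each page it says "This plastic bangle will be given to the health worker with instruction for use" and lists the measuring steps, ending with noting the intensity.

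Section 5.2 requires staff to "Provide a diary card (DC1) to the subject or parent/guardian (s) and inform them how to use and fill the diary card" and to "Keep the subject under observation for 30 minutes and evaluate the immediate local reactions and systemic events". Section 3.6 provides one home device: "subject/parent will be supplied with a thermometer and instructed how to use it".

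Section 8.1.3.2 plans to report local reactions within 72 hours of each injection, and from 72 hours to one month, "global and broken down according to the size of the reaction when appropriate".

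**The concern.** One section says the family measures; the appendix that describes the tool gives it, with its instructions, to staff. The difference matters because the size grade cannot be applied without the tool, and because staff have no scheduled chance to use it during most of the 72-hour period.

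What is at stake is the severity grading of size-graded local reactions. Safety is a secondary objective in all subjects and is also compared descriptively between QIV and TIV and between the three batches. If a grade was never measured while the reaction was present, no later analysis can recover it. The statistical analysis plan cannot repair this, because it is a matter of data collection.

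**Working it through.** No sample size, power or alpha figure is involved. The check sets the passages side by side and does the window arithmetic.

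1. **Who measures and records.** Section 6.3: parents or subjects, with the bangle. The code goes in the diary, which Section 3.6 has subjects keep for 28 days, and in the CRF. Section 7.2.2 also has the investigator assess intensity, and has 72-hour reactions evaluated by interview at the visits.

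2. **Who is given the bangle.** Appendix 3, both pages: the health worker. No other recipient is named there.

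3. **What families are given.** Section 5.2 and the Schedule & Activities table: diary cards. Section 3.6: a thermometer. Section 3.7 lists protocols, CRFs and diaries as clinical supplies. None of these mentions a bangle. Section 6.3 points to Appendix 4 for it, but the bangle is in Appendix 3 and the list in Section 12 ends at Appendix 3, so the cross-reference does not settle the matter.

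4. **Whether the grade can be applied without the bangle.** The Section 6.3 table refers to the smaller and larger circles and gives no diameters. These appear only in Appendix 3 and differ by age group: 5 cm and 10 cm for Groups II and III, 2.5 cm and 5 cm for Groups I, IV and V. On the text available, a family without the bangle has no cut-off.

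5. **Scheduled contacts after an injection.**
   - 0 to 30 minutes: in person (Section 5.2). Staff can use the bangle.
   - Day 3: by phone (Section 3.6, stated as V1+3 days). No measurement is possible.
   - Next visit: 28 (-4/+7) days after the dose (Section 5.2). Earliest 28 - 4 = Day 24; latest 28 + 7 = Day 35.
   - Gap from the close of the 72-hour period to that visit: 24 - 3 = 21 days to 35 - 3 = 32 days.
   - The synopsis and Section 3.4.4 count V3 from Day 0 instead (56, -4/+7 days). On that reading the shortest interval from dose 2 to V3 is 52 - 35 = 17 days, which is still far outside 72 hours, so the result is the same.

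6. **How many are covered by the instruction.** Subjects: 540 + 270 = 810. Injections: 540 x 1 + 270 x 2 = 1,080. These are ceilings. Only subjects with redness, swelling, induration or another local reaction need a size grade. The earlier studies in Section 1.5 report any local reaction in 20.0% (trivalent, adolescents and adults) and 85.5% (two subcutaneous doses of a quadrivalent vaccine, adults). Neither figure separates pain from size-graded reactions, so they do not give the affected number.

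7. **Which outputs use the bangle.** The safety criteria in Section 7.2.1 count subjects with at least one event by period, and serious adverse events; none needs a size. Pain, fever, fatigue and myalgia have their own grading rows. Only the size breakdown in Section 8.1.3.2 depends on the circles.

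**The case against.** The strongest reply is that Section 6.3 already settles who measures. It names parents and subjects and puts the code in a diary that they keep, so home measurement is clearly intended and Appendix 3 is merely incomplete about distribution. The visit lists in Section 5.2 are no proof to the contrary: they also omit the thermometer and the Day 3 call, both of which Section 3.6 provides for. Staff must explain the diary card, and the card itself is not among the documents, so it may carry the instruction. Finally, the size breakdown is descriptive, is reported where appropriate, and sits within a secondary criterion.

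Much of this stands, and it limits the point. A reader might infer any of four stronger things:

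- **That Appendix 3 confines the bangle to the health worker.** It does not say so. The health worker is the sole named recipient, and passing the tool on is not excluded.
- **That 72-hour size grades cannot be obtained at all.** This is conditional on following Appendix 3 as written. If Section 6.3 prevails and families receive the tool, the grades can be obtained. Staff can measure reactions in the first 30 minutes in any case, and an unscheduled visit is possible.
- **That severity data for all 810 subjects are compromised.** The instruction covers all of them, but only size-graded reactions are exposed.
- **That assessors will differ between recruitment sites.** The trial has one centre recruiting at a hospital and three health centres, and nothing in the Protocol shows that practice would differ among them.

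What the reply does not remove is that two sections give different instructions about the tool and no text puts it in the family's hands. The thermometer sentence in Section 3.6 shows that the Protocol can state home supply of a device explicitly; for the bangle it does not.

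**Conclusion.** The inconsistency is real and should be corrected. If Appendix 3 is followed as written, redness, swelling, induration and other local reactions arising after the 30-minute observation and within 72 hours have no scheduled contact at which they could be graded with the bangle, and the 72-hour size breakdown would rest on estimate or on recall 24 to 35 days after the dose.

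The effect is confined to that descriptive breakdown. The primary criterion (HI titre), the numbers and percentages of subjects with reactions, the pain grades and the systemic grades do not depend on the bangle. The number of reactions affected is unknown.

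The conclusion assumes that the diary card, which cannot be checked here, does not itself supply the bangle or its diameters, and that no unscheduled visit takes place.

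**What to change.** Reconcile Section 6.3 with Appendix 3:

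- On both pages of Appendix 3, state that the bangle for the subject's age group is given to the subject or parent, with instruction in its use, together with DC1, and with DC2 for Groups IV and V.
- In Section 5.2, add issue of the bangle and instruction to the diary-card steps at Visit 1 (both sub-studies) and Visit 2 (Sub-study B).
- Keep health-worker use of the same bangle for the 30-minute check and for any reaction still present at a visit.
- In Section 6.3, correct both references to Appendix 4 so that they read Appendix 3.

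The cost is a few lines of text and one plastic square per subject: 810 if families in Groups IV and V keep theirs for the second dose, or at most 810 + 270 = 1,080 if a new one is issued with DC2.
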